Despite these improvements, gaps still exist, especially in the long term follow-up of women after successful fistula repair [17]. In fact, data currently available show that delivery leading to fistula usually ends up with a stillbirth [10–12] and that women are relatively young at the time their fistula is repaired [3]. Therefore, when successfully repaired, women return to their community with the desire to resume social and sexual life, and have children [18–20]. However, this return to sexuality exposes repaired woman to pregnancy and childbirth, which increases the risk of recurrence of a previously repaired fistula or the formation of a second, new fistula [18, 19]. Fear of recurrence of fistula is a constant worry for women successfully repaired of OF [21–23] and, given the cost of fistula care and the lower success of repairing [24], these women might need more attention to prevent recurrence of fistula and adverse pregnancy outcomes.

There is no precise estimate of the recurrence of fistula or pregnancy after OF repair. In Ethiopia, Nielsen et al [18] observed 2.63 % re-occurrence of fistula among 38 women in a 21 months’ post-repair median follow up and Browning and Menber [19] recorded 4.26 % in 141 women successfully repaired after 6 months’ follow-up. In Malawi, Wilson et al [20] reported 3.85 % of re-occurrence in 26 women after 9 − 24 months’ follow-up post-repair.

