### Sample size calculation

For the estimation of the incidence rate of the recurrence of fistula, we used the 2-Sided Confidence Intervals for 1 Proportion Confidence Interval Formula [31]. Using the existing data [19] and considering a +/- 2 % margin of error and 95 % confidence interval, we estimate the sample size of the cohort to be 280. We anticipate 20 % loss to follow-up and 10 % refusal rate and accordingly increase the sample size to 364. The same formula provides an estimation of the sample size for the incidence rate of pregnancy [31]. If we estimate the rate of pregnancy to be around 20 % at 24 months’ follow-up among successfully repaired women [20], a sample size of 264 women produces a 2-sided 95 % confidence interval with 10 % precision. Therefore, the sample size of 364 women will be sufficient to describe the objective on pregnancy and its outcomes.

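### The recurrence sample size of 280 does not follow from its visible inputs (4.26 %, ±2 points, 95 % give at least 392), and the inflation to 364 multiplies where it should divide

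*Protocol article*

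**What the plan says.** The section on sample size calculation in the protocol article names its method, "we used the 2-Sided Confidence Intervals for 1 Proportion Confidence Interval Formula", and gives the inputs and result for recurrence in one sentence: "considering a +/- 2 % margin of error and 95 % confidence interval, we estimate the sample size of the cohort to be 280". The rate is not printed there; it is taken from reference 19. The Background reports that source as having "recorded 4.26 % in 141 women successfully repaired" with 6 months of follow-up.

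The next step is: "We anticipate 20 % loss to follow-up and 10 % refusal rate and accordingly increase the sample size to 364".

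For pregnancy, the same formula is said to apply. With an expected rate of about 20 % at 24 months, "a sample size of 264 women produces a 2-sided 95 % confidence interval with 10 % precision", and 364 is then declared enough for pregnancy and its outcomes. The Abstract gives 364 as the sample size, and the Discussion lists the sample size among the study's strengths.

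**The concern.** All the inputs to the recurrence calculation are either printed or traceable within the article, so a reader can repeat it, and the result is not 280. This is the only quantitative justification for the primary outcome. If the planning rate is the one cited, the interval will be wider than the ±2 points announced. The inflation step has a separate fault that can widen the gap, and how far depends on whether 364 means women approached or women enrolled, which the text does not settle. In the pregnancy sentence, precision has to be read differently from the ± margin earlier in the same paragraph for its number to reproduce.

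**Working it through.** **Inputs.** p = 0.0426 (Background, reference 19; 6/141 = 4.26 %). Half-width d = 0.02, two-sided 95 % (z = 1.96), refusal 10 % and loss 20 % (sample size section).

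**1. Trying to reproduce 280.** Formula: n = z²·p(1−p)/d².

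- p = 0.0426: 3.8416 × 0.0426 × 0.9574 / 0.0004 = 391.7, so 392.
- p = 0.03: 279.5, so 280. The rate of 3 % is not in the article.
- The other recurrence rates in the Background: 2.63 % gives 246; 3.85 % gives 356.
- A 90 % interval at 4.26 % gives 276, but the text says 95 %.
- A finite population correction is not mentioned. With 400–450 repairs a year (Specific setting) over 3.5 years, N = 1,400 to 1,575, and n = 391.7/(1 + 390.7/N) = 306 to 314.

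Other two-sided 95 % methods at 4.26 % with total width 4 points give 407 (Wilson), 424 (Agresti-Coull), 441 (Wald with continuity correction), 444 (Clopper-Pearson) and 454 (Wilson with continuity correction). So 392 is the most lenient of the standard answers.

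**2. Inflation.** The article's figure is 280 × 1.30 = 364. To keep 280 after both losses, one divides: 280/(0.9 × 0.8) = 280/0.72 = 388.9, so 389 approached. What 364 delivers depends on what it counts:

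- women approached: 364 × 0.9 × 0.8 = 262;
- women enrolled: 364 × 0.8 = 291.

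**3. Precision at 4.26 %.** Half-width = 1.96·√(0.0426 × 0.9574/n).

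| Evaluable women | Half-width (points) |
|---|---|
| 262 (364 approached) | ±2.45 |
| 280 (stated) | ±2.37 |
| 291 (364 enrolled) | ±2.32 |
| 364 (no loss at all) | ±2.07 |

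Clopper-Pearson intervals are wider: half of the total width is 2.65, 2.56 and 2.22 points at 262, 280 and 364.

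**4. The same at 3 %.** 1.96·√(0.03 × 0.97/n) gives ±2.00 with 280, ±2.07 with 262 and ±1.96 with 291.

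**5. Pregnancy.** At p = 0.20, a Clopper-Pearson interval of total width 10 points needs 263.7, so 264. That reproduces the article's figure, with 10 % as total width (about ±5). A Wald interval of ±10 points would need only 62. Expected pregnancies are 0.20 × 262 = 52 or 0.20 × 291 = 58. For an outcome proportion near 50 %, the half-width is 0.98/√52.4 = 0.135 or 0.98/√58.2 = 0.128, about ±13 points.

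**The case against.** The strongest reply is that this shows a calculation that cannot be reproduced, not a proven loss of precision. The sample size section does not print 4.26 %. The Background also gives 4.26 % for pregnancy in the same source, so one of the two might be a slip. If 3 % was the rate used, 280 is right and the defect is an unstated input. This stands as a limit: a reader might infer that the study will certainly miss ±2 points, but that holds only if the recurrence rate is about 4.26 % or higher. It does not rescue the paragraph, which points to a source whose recurrence rate the article gives as 4.26 %.

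Three further inferences go too far.

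- **That the expected 262 falls short of the 264 given for pregnancy.** This is true only if 364 counts women approached. The Abstract calls 364 the sample size, and women who refuse are excluded; if 364 are enrolled, 291 remain, above both 280 and 264.
- **That 264 is too few.** It is not, under either reading of precision. The fault there is mainly wording.
- **That recurrence by 48 months will be well above 4.26 %, with much wider intervals.** Cumulative incidence cannot fall within a cohort, but the longer follow-ups cited in the Background show 2.63 % (median 21 months) and 3.85 % (9–24 months). Those samples are small (38 and 26 women), yet they give no support for a markedly higher figure. What stands is that a 6-month rate is used for an objective that runs to 48 months, so the precision may differ.

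Finally, women lost to follow-up are censored in the time-to-event analysis and contribute information until then. The half-widths above treat them as contributing nothing, so they are approximate and somewhat pessimistic on this count.

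**Conclusion.** Wrong as written. At 4.26 %, ±2 points and two-sided 95 %, at least 392 evaluable women are needed, which is 112 more than stated. The expected half-width is about ±2.3 to ±2.5 points under the article's own attrition, and ±2 is not reached even if all 364 women are retained. The inflation is a separate error: 389 women approached, not 364, are needed to keep 280. These conclusions rest on 4.26 % being the planning rate and on a simple proportion as the estimate; under an unstated 3 % the figure of 280 is correct.

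The shortfall is about 0.3 to 0.5 of a point in a descriptive estimate with no hypothesis test behind the number. The paragraph should be corrected, but the study does not fail because of it.

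**What to change.** Rewrite the sample size paragraph as follows.

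- State the planning rate actually used. If it was 3 %, say so and justify it; otherwise keep 4.26 % and give the precision that follows.
- Say whether 364 is the number approached or enrolled.
- Correct the inflation by dividing by the retained fraction, and give the evaluable number that results (about 262 or 291).
- Restate the expected precision for recurrence as about ±2.3 to ±2.5 points at 4.26 %.
- Note that 4.26 % is a 6-month rate while follow-up runs to 48 months, so the precision reached may differ.
- For pregnancy, write that 264 corresponds to a total width of 10 points (about ±5). Add that about 52 to 58 pregnancies are expected, so outcome proportions near 50 % would carry about ±13 points.

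The cost is one reworded paragraph and a slightly less favourable stated precision. No additional women are needed.

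### The base sample size of 280 does not follow from its stated inputs: at the 4.26 % recurrence reported for the cited study, a two-sided 95 % interval of +/-2 points needs 392 to 444 women

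*Protocol article*

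**What the plan says.** The Sample size calculation section names its method: "we used the 2-Sided Confidence Intervals for 1 Proportion Confidence Interval Formula [31"]. It then gives the inputs and the result. The inputs are introduced with "Using the existing data [19] and considering a +/- 2 % margin of error and 95" per cent, and the sentence ends with the "confidence interval, we estimate the sample size of the cohort to be 280". The next sentence carries this figure forward: "We anticipate 20 % loss to follow-up and 10 % refusal rate and accordingly increase the sample size to 364".

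The section does not write out the planning rate. The Background does report it for study [19], an Ethiopian follow-up study, which "recorded 4.26 % in 141 women successfully repaired after 6 months" of follow-up. No other recurrence rate is attributed to that study anywhere in the article.

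The section also sizes the pregnancy objective: "The same formula provides an estimation of the sample size for the incidence rate of pregnancy". It assumes 20 % and arrives at 264 women for a precision of 10 %.

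**The concern.** All the terms of a one-proportion precision calculation can be read from the article: the rate (through study [19]), the margin, the sidedness and the confidence level. Put together, they do not give 280.

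Recurrence is the primary outcome, and the +/-2 % margin is what the article offers as justification for the size of the cohort on that outcome. If 280 is too small for the margin, readers are promised a tighter primary estimate than the design gives at its own planning rate. The discrepancy also carries into 364, which is 280 x 1.30.

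**Working it through.** **Inputs**

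- Rate p = 0.0426 (Background, 4.26 % of 141 women, study [19]); p(1 - p) = 0.0426 x 0.9574 = 0.040785.
- Margin d = 0.02, two-sided 95 %, so z = 1.96 (Sample size calculation).
- Stated result: 280, raised to 364.

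**Step 1: try to reproduce 280**

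Wald: n = z² p(1 - p) / d² = 3.8416 x 0.040785 / 0.0004 = 391.7, so 392.

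The article does not name the interval variant, so two other common ones were tried. The smallest n with a total width of at most 4 points at p = 0.0426 is:

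| Interval | n needed | Shortfall of 280 |
|---|---|---|
| Wald | 392 | 1 - 280/392 = 29 % |
| Score (Wilson) | 407 | 1 - 280/407 = 31 % |
| Exact (Clopper-Pearson) | 444 | 1 - 280/444 = 37 % |

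Jeffreys (396), Agresti-Coull (424) and the continuity-corrected Wald (441) and Wilson (454) intervals were also tried. None gives 280.

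**Step 2: what precision the planned numbers give at 4.26 %**

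- 280 evaluable: Wald half-width 1.96 x sqrt(0.040785/280) = 0.02365, about 2.37 points. The exact interval is 2.2 % to 7.3 %, about 5.1 points wide instead of 4.
- 364 evaluable, with no loss at all: Wald half-width 1.96 x sqrt(0.040785/364) = 0.02075, about 2.07 points. The exact interval is 2.4 % to 6.9 %, about 4.4 points wide.

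**Step 3: which rate would give 280**

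- Wald: 3.8416 x 0.03 x 0.97 / 0.0004 = 279.5, so 280 at 3 %.
- Score interval: 278 at 2.7 %.
- Exact interval: 281 at 2.4 %.

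None of these rates is stated in the article. The two other recurrence rates in the Background do not give 280 by Wald either: 2.63 % (38 women) gives 246 and 3.85 % (26 women) gives 356.

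**Step 4: other possible origins**

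- A two-sided 90 % level at 4.26 % gives 276 (Wald) or 280 (Jeffreys), but the article says 95 %.
- A finite population correction, n = 392 / (1 + 391/N), is not mentioned. With the article's 400 to 450 repairs a year over 3.5 years (N = 1400 to 1575) it gives 307 to 314.

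**Step 5: the pregnancy figure**

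At 20 % with a total width of 10 points, the exact interval needs 264 (Wald 246). The stated 264 is therefore reproduced. Read as +/-10 points, the answer would be 62 (Wald) or 70 (exact).

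**The case against.** **The planning rate is inferred.** The Sample size calculation section cites study [19] without printing a rate, and that study may contain another figure, such as one for a subgroup. This stands as a limit on the claim. If a lower rate was used, the arithmetic may be right and the input undisclosed. It does not rescue the text, because 280 cannot be obtained from the only recurrence rate the article reports for the study it cites.

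**The consequence is small.** With all 364 women evaluable, the Wald miss is 0.07 points. That is fair for 364. But 364 includes the allowance for loss and refusal, and the plan relies on 280 to give the margin; there the half-width is about 0.37 points too wide. It is also true that this is a descriptive cohort, that the primary estimate will have its own interval, and that the planning margin biases nothing.

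**Stronger readings that the article does not support**

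- A reader might infer that the authors used 3 %. That is only the Wald back-solution; the score and exact intervals point to about 2.7 % and 2.4 %.
- A reader might infer that 280 and 264 must come from different formulas, despite the article's statement that the formula is the same. This does not follow: the exact interval gives 264 for pregnancy and about 281 for recurrence at an unstated 2.4 %.
- A reader might call 264 an error. It is reproducible if 10 % precision means total width, so only its wording is ambiguous.
- A reader might say the +/-2 % margin is the only justification for the sample size. The pregnancy calculation is a second one and is unaffected.

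**Conclusion.** The point holds. As written, 280 does not follow from study [19], +/-2 % and two-sided 95 %: the stated inputs require 392 (Wald), 407 (score) or 444 (exact) women. At 4.26 % the stated primary precision is not delivered by 280 women (about +/-2.37 points, exact 2.2 % to 7.3 %). It is narrowly missed by Wald even with all 364 evaluable (+/-2.07 points, exact 2.4 % to 6.9 %).

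This rests on one assumption, that the planning rate was the 4.26 % the article reports for study [19]. If another rate was used, the fault is an undisclosed and unsourced input instead. In both cases the paragraph needs correcting. The error concerns the stated precision of the primary estimate. It does not invalidate the cohort or its analysis.

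**What to change.** Change the recurrence part of the Sample size calculation section in one of two ways.

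1. Keep 280 and restate the precision, for example: *At an expected recurrence of 4.26 %, 280 evaluable women give a 95 % confidence interval of about +/-2.4 points (exact interval 2.2 % to 7.3 %).*
2. If another planning rate was used, state it with its source and show that it gives 280 for +/-2 points. By Wald it would be about 3 %; by the score or exact interval about 2.7 % or 2.4 %.

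In either case, name the interval method. As a matter of wording only, say whether the 10 % precision for pregnancy is the total width (+/-5 points), which is the reading under which 264 is reproduced.

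No extra enrolment is needed. The cost is a rewritten paragraph and, under the first option, a slightly less favourable stated precision.

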### Participants’ recruitment and follow-up

All women who underwent successful repair of OF from January 1, 2012 to June 30, 2015 at the 3 study sites are eligible for inclusion in study. However, only women with a unique obstetric fistula that was closed at discharge, as measured by a dye test, who provide written informed consent, reside in Guinea and agree with follow-up visits will be included in the study (Fig. 1). Eligible participants who refuse informed consent, who got repair outside the study sites or whose medical records are incomplete will be excluded.

Individual medical records of all women who benefited fistula repair at the 3 sites in 2012–2015 will be screened by the study team to identify those who were discharged with a close fistula (Fig. 1). After locating them through their medical records, the study team (that includes nurses called “Fistula Counsellors” who are involved in the management of women at the fistula repair sites) will contact women by home visit in their community to obtain informed consent.

Once the informed consent is obtained, the woman will be interviewed for 30 − 60 min by the study team and examined in an isolated place for inclusion in the study. Later, her medical records will be used at the fistula repair site where she got the surgery to collect her sociodemographic and clinical characteristics at the time of surgery. For all women recruited in the study, most retrospectively, new fistula or recurrence of the repaired fistula, pregnancies and their outcomes (miscarriage, stillbirth, live birth, early new-born death, maternal death, and type of maternal complication) will be documented. Health Centres and Health posts around which the study participants live will be used by the study team to perform the dye test in women who report “Continuous and uncontrolled leaking” since discharge or at the follow up visit.

### Study procedures

The study team will retrospectively screen individual medical records of all women who benefited fistula repair at the 3 sites from January 1, 2012 to June 30, 2015 to identify those who were discharged with a close fistula (Table 1 and Fig. 2).

**Table 1 Tab1:** Study schedule of assessment

Study steps	Procedures
*Screening*	• Retrieving of medical records • Identification of women closed at discharge
*Enrolment*	• Home visit to seek informed consent • Administering of inclusion questionnaire • Dye test at nearest health post/centre • Appropriate referral when needed • Collection of demographic and clinical data from medical records
*Follow up visits*	• Home visit to administer follow up questionnaire • Dye test at nearest health post/centre • Appropriate referral when needed

**Fig. 2 Fig2:**
[figure not shown]
Study timeline

A home visit will then be conducted within the community to seek informed consent with the repaired women. After obtaining the consent, women will be interviewed. Women who report “Continuous and uncontrolled leaking” since the last follow-up visit will be scheduled for a pelvic exam and a dye test at the nearest health centre or health post. If the case is confirmed as fistula (by a dye test of clinical exam), the woman will be counselled and referred to the nearest fistula repair centre. By this approach, we think that any misclassification of outcome (recurrence of fistula) will be minimal, since women with any continuous and uncontrolled leakage of urine following repair are likely to report it, and any reported incontinence will be evaluated by a dye test.

If a woman reports pregnancy, she will be asked to show her antenatal care (ANC) & delivery card on which pregnancy test result is routinely reported. If possible, a pregnancy test will be performed. Otherwise, investigators will rely on woman self-reporting.

Sociodemographic and clinical characteristics of women will be collected from individual medical records at each participating fistula repair site.

All investigators will receive appropriate training at the Maferinyah National Research and Training Centre before they go in the field.

### Data collection

#### Recruitment and follow-up visit

The enrolment and follow up data are collected using structured and pre tested standardised questionnaires. Both questionnaires will include participants’ current fistula status (fistula close and continent/closed but not continent), post-operative social and reproductive life (marital status, occupation, sexuality, use of modern contraceptive methods, pregnancy, childbirth), and any fistula related complication. Participants’ current full address is also collected to facilitate communication, referral and follow-up visits.

#### Sociodemographic and clinical characteristics

After obtaining the informed consent during the recruitment visit, a standardised questionnaire called Baseline form is used to collect the demographic and clinical characteristics of women from hospital records in the hospitals where they were discharged from. This questionnaire includes age at presentation at hospital, marital status, age at marriage, occupation, level of education, residence (rural/urban), number of pregnancies, parity, number of previous repairs, and duration of fistula. Clinical characteristics include mode of delivery related to development of the fistula, neonatal outcome at causal delivery, type of fistula (VVF, RVF or both), status of the bladder neck, nature of the fistula according to the surgeon (simple versus complex), duration of catheterization after repair, status of the operating surgeon (expatriate, local trainer, local trainee), postoperative complications, context of repair (routine repair or pooled repair) and the status of the fistula at discharge (close and continent/Close but not continent).

### Data management

Study forms will be checked after data collection before sending to the Maferinyah Training and Research Centre in a sealed envelope where they will be stored in a locked cabinet. Data will be double entered by 2 independent encoders into a data entry file created using EpiData Entry software (EpiData Association, Odense, Denmark). Reliability will be checked and any inconsistencies in data entry will be resolved. It is planned to perform data entry on a continuous basis from the start of enrolment so that discrepancies are addressed while data collection is ongoing. Data entry screens will be created for each form used in the study. The database will be password protected and only authorized users will be given access. All data will be stored in a GCP compliant server, and data management will respect patient confidentiality.

All study documents with the participant’s name (i.e. participants’ contact form) will be kept in a strict confidentiality.

### Data analysis

Categorical data and treatment outcomes will be summarized as frequencies (%) and compared using *χ*2 or Fisher’s exact tests as appropriate. Continuous data will be presented using median (interquartile range) and compared using the Wilcoxon rank-sum test. Follow-up will be calculated from the date of hospital discharge. The date of fistula recurrence or the estimated date of pregnancy will be selected as the date of events. Patients who do not experience recurrence of fistula or pregnancy will be censored at the last follow up visit. For patients who are reported dead (by the relatives), the date of death will be used to determine their follow-up time in the study. For patients who are lost to follow up (i.e. who move from their village without any address to joint them after inclusion) the date of the last visit will be used.

Socio-demographic and clinical differences between those women who remain in the study and those who are lost-to-follow-up will be estimated to check for any imbalances at inclusion.

The incidence of fistula recurrence and that of pregnancy will be estimated using the method of cumulative incidence. The cumulative incidence rate will be compared across risk factors using Kaplan-Meier methods. Exposure variables with a *P*-value <0.2 in the univariate analysis will be included in multivariate models. Exposure variables with a *P*-value <0.2 in the univariate analysis will be included in multivariate models. A risk factor analysis will be performed using adjusted Cox regression. Associations will be reported as adjusted hazard ratios with 95 % CIs. Analysis will be done using STATA version 12 (STATA Corporation, College Station, TX, USA) with a level of significance will be set at *P* < 0.05.

For the outcomes of pregnancy (miscarriage or abortion, mother and child status at delivery), Pearson’s Chi square (*χ*2) will be used to compare proportions of these outcomes between potential exposure variables (age group, previous repair (Yes/No), fistula status at hospital discharge, use of antenatal care, delivery by caesarean section, etc.). Logistic regression analysis and models will be used and associations will be reported as risk ratios with a level of significance set at *P* = 0.05 and a 95 % confidence intervals.

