**Fig. 1 Fig1:**
[figure not shown]
Study flow chart

The primary outcome is the incidence rate of the recurrence of fistula. For the purpose of this study, recurrence of fistula includes the breakdown of a repaired fistula or the occurrence of a new fistula in study participants. At the study sites, the closure of fistula was determined at hospital discharge by a pelvic exam using a dye test. During follow-up visits, women will first be asked about current medical status using the question “does the woman have continuous and uncontrolled leakage of urine?”. If the answer is “YES” then women will be scheduled for a pelvic exam with a dye test for confirmation, at the nearest health facility (health centre or health post). This question is always used at EngenderHealth supported sites to assess women at reception, before further pelvic exam. In addition, the presence of “continuous and uncontrolled leakage of urine” is commonly used as a screening question for fistula in circumstances in which a pelvic exam is not possible (e.g. Demographic and Helath Surveys, DHS); it differentiates between fistula and other forms of incontinence, which are unlikely to be continuous and uncontrolled. In some cases, it might not be feasible to perform the dye test if for instance the woman refuses to go to a health facility. This might lead to a misclassification which can bias the estimate towards a null. However, misclassification is unlikely, since women with continued urinary leakage are eager to report their experiences in order for the condition to be rectified.

The secondary outcomes include pregnancy and pregnancy and outcomes (miscarriage or abortion or term pregnancy). Pregnancy and pregnancy outcomes will be documented by a positive pregnancy test from discharge (done at recruitment or during follow-up visit or given at any time by a result from medical records such as antenatal (ANC) card) or by a self-reporting corroborated by 2 witnesses. Maternal status at delivery and mode of delivery (dead or alive; caesarean section or normal delivery; no complication or any complication) will be assessed by looking at the ANC & Delivery card or hospital records or self-reporting. Child outcome at delivery (stillbirth, neonatal death or alive) will be assessed by looking at the ANC & Delivery card or hospital records or self-reporting corroborated by 2 witnesses.

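### Pregnancy is dated back to its estimated start but event-free women are censored at the last visit, so pregnancies not yet recognised then count as pregnancy-free time and the late part of the curve is biased down (minor)

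*Protocol article*

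**What the plan says.** All references are to the protocol article.

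- **Time origin** (Data analysis): "Follow-up will be calculated from the date of hospital discharge".
- **Event date** (Data analysis): "The date of fistula recurrence or the estimated date of pregnancy will be selected as the date of events".
- **Censoring** (Data analysis): "Patients who do not experience recurrence of fistula or pregnancy will be censored at the last follow up visit". For women lost to follow-up, "the date of the last visit will be used".
- **How a pregnancy is found** (Study procedures): "If a woman reports pregnancy, she will be asked to show her antenatal care (ANC) & delivery card". The text continues: "If possible, a pregnancy test will be performed. Otherwise, investigators will rely on woman self-reporting".
- **What counts as documentation** (Study design): "Pregnancy and pregnancy outcomes will be documented by a positive pregnancy test from discharge". The test may be done at recruitment, at a follow-up visit, or be taken from medical records. Self-report backed by two witnesses is the alternative. No sentence requires a test of every woman at every visit.

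The article states no recognition lag, no cut-off before the last visit, and no look-back after it.

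**The concern.** The event date and the censoring date use different clocks. A pregnancy event is placed at its estimated start, some time before anyone knows of it. Event-free time runs right up to the last visit. A woman who conceived shortly before that visit and does not yet know it reports nothing, and is recorded as pregnancy-free over a stretch in which her event has already occurred.

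At earlier visits this corrects itself, because the next visit picks the pregnancy up and dates it back. After the last visit nothing does. The final weeks of each event-free woman's follow-up are counted in full as time at risk although almost no event can be recorded in them.

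Follow-up closes on one calendar date (30 June 2016). Among women still under observation, the share who are close to their own last visit therefore rises with time since discharge. The loss of events concentrates at the long end of the curve, near the 48-month horizon named in the study's second objective. The risk is a curve that flattens late for a reason unrelated to fertility.

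**Working it through.** **Inputs from the article.** Pregnancy 20 % at 24 months (Sample size calculation). Repairs from 1 January 2012 to 30 June 2015 and follow-up to 30 June 2016, which is 12 to 54 months by the calendar. Stated maximum follow-up 48 months (Abstract). Planned N = 364.

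**The plan's own figure first.** The only number tied to the pregnancy endpoint is N = 264. An exact (Clopper-Pearson) 95 % interval for 20 % with a total width of 10 points gives n = 264, so it reproduces. It shows that the plan's 10 % precision means a total width of 10 points, or about 5 points either side.

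**Assumptions, not in the article.** Constant hazard; last visits uniform over 12 to 54 months; a conception within L months of the last visit goes unrecorded; L = 0.5, 1, 2 or 3 months.

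**Step 1: true curve.** Hazard = -ln(0.8)/24 = 0.0093 per month. Cumulative incidence at t months is 1 - 0.8^(t/24): 20.0 % at 24 months and 1 - 0.8² = 36.0 % at 48 months.

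**Step 2: share of the hazard that is seen.** At time t it is approximately P(last visit > t + L) / P(last visit > t) = 1 - L/(54 - t) for t between 12 and 54 - L. Integrating the loss from month 12:

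- by month 24: L × ln(42/30) = 0.34 L months of hazard lost;
- by month 48: L × ln(42/6) = 1.95 L months lost;
- within months 36 to 48: L × ln(18/6) = 1.10 L months out of 12, which is 9 % at L = 1 and 27 % at L = 3.

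**Step 3: estimated curve.** Put 24 - 0.34 L and 48 - 1.95 L into 1 - 0.8^(m/24). For L = 1 at 48 months: 1 - 0.8^(46.05/24) = 34.8 %. Simulation with 1,000,000 women per scenario agrees with the formula to within about 0.2 points. In the table, the 24-month column and the last column are simulated. The middle column is the formula, with the simulated value in brackets where it differs.

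| L (months) | 24 months (true 20.0 %) | 48 months, visits to 54 (true 36.0 %) | Near 48 months, less favourable visit timing |
|---|---|---|---|
| 0.5 | 19.9 | 35.4 | 35.1 |
| 1 | 19.7 | 34.8 | 34.3 |
| 2 | 19.4 | 33.6 (33.5) | 32.7 |
| 3 | 19.1 | 32.4 (32.2 to 32.3) | 31.1 |

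The last column is the low end across alternatives: follow-up capped at the stated 48 months, or last visits falling 0 to 6 months before study end. With the cap and L = 2, only 59 % of the hazard in months 42 to 48 is observed, and none in the last month.

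**Step 4: against sampling error.** With N = 364 and no loss, the standard error of the 48-month estimate is about 3.5 to 3.7 points, a 95 % half-width of about 7. The bias at 48 months (about 0.6, 1.2, 2.5 and 3.7 points) runs from a small fraction of one standard error to about one.

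**Step 5: the correction.** Cutting events and censoring at the last visit minus L returns 20.0 % at 24 months and about 36 % at 48 months when visits run past 48 months. With the 48-month cap the corrected curve is unbiased but can be read only to 48 - L. For 12 weeks (about 2.8 months) that is about month 45.

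**The case against.** The strongest counter-case has five parts.

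1. *The article never says conception.* True. It is an inference from the estimated pregnancy date. It is the natural reading, and any back-dated start gives the same direction of bias.
2. *Pregnancy is not left to chance recall.* Both questionnaires cover pregnancy (Data collection), and the Study design section lists tests at recruitment or follow-up visits. A reader might infer that a pregnancy is never sought unless the woman volunteers it; the article does not support that. Nor does it support routine testing of every woman, since Study procedures makes the test conditional on her report and on feasibility. If testing were routine, the lag would shrink to about half a month and the 48-month bias to about 1 point or less.
3. *The lag is assumed.* This stands. The upper figures need essentially every woman to be unaware, and untested, for three full months.
4. *Correction costs precision.* This stands. In simulation at N = 364 the root mean square error at 48 months under the stated rule is about 3.7, 4.3 and 5.1 points for lags of 1, 2 and 3 months, against about 4.2 with a 3-month cut-off. That cut-off is worse on this measure at 1 month, even at about 2, and better at 3. What it buys throughout is removal of an error that always runs one way.
5. *A condensed article may leave a cut-off to the full plan.* It may, but this article states both the event-date rule and the censoring rule, and the bias follows from applying them as written.

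**Conclusion.** The concern holds as a minor point on a secondary endpoint. The direction follows from the stated rules for any recognition lag above zero: the pregnancy curve is too low, mainly late in follow-up. The size depends on the assumed lag of 0.5 to 3 months, the constant hazard and the spread of last visits. On those assumptions it is about 0.1 to 1 point at 24 months and 0.6 to 4 points near 48 months, rising to about 4.9 points (36.0 - 31.1) at a 3-month lag under less favourable visit timing.

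Three stronger readings are tempting and not supported. One is that the 48-month estimate is known to be about 4 points low, or that a quarter of the late hazard is known to be lost; both need the longest assumed lag, and the article gives none. A second is that an earlier cut-off recovers the full 48-month estimate; that is so only if visits run past 48 months, which the calendar dates allow but the stated maximum does not. A third is that the study's main result is affected. The primary outcome is recurrence, which this mechanism does not touch; the proportions for pregnancy outcomes do not use the curve; and no effect on the Cox hazard ratios has been shown.

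**What to change.** Add one rule to Data analysis, for time to pregnancy only. Follow-up ends at the last visit minus a prespecified recognition lag, for example 8 to 12 weeks, or shorter if every woman is tested at that visit. Count only pregnancies whose estimated start falls before the cut-off, and censor all other women at the cut-off. Events and censoring must be cut alike; moving only one of them creates a new bias.

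Report the uncut analysis, or one with a different lag, as a sensitivity analysis. State that the curve is read only to the maximum follow-up minus the lag, which is about month 45 with a 48-month cap and 12 weeks. Say which maximum applies, since the stated 48 months and the 54 months allowed by the calendar dates differ. Leave censoring for recurrence at the last visit.

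The cost is a few weeks of person-time per woman, the few pregnancies recognised within those weeks, and about 0.2 to 0.7 points of extra standard error at 48 months. Under the cap, the last weeks of the 48-month horizon are also given up. No new data are needed.
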